### Participant recruitment and baseline assessment

The study will take place in approximately ten schools across England. All schools will be comprehensive secondary schools and have a standard Sex and Relationships (SRE) policy and SRE curriculum in place.

Researchers will make contact with SRE co-ordinators at the schools who will describe the study and invite participation. SRE co-ordinators who wish to participate will be required to obtain permission from the school head teacher. They will be asked to identify classes receiving SRE in their school where pupils are aged 13–16 years old. SRE teachers must confirm that the chlamydia lesson has not previously been delivered to these pupils and that they have not received any teaching on STIs. Full details on the requirements of participating schools will be provided. Schools will be offered a £100 Amazon voucher in recognition of the time and resource commitment required. They will also be offered an individual school report based on anonymised and aggregated pupil data from this study which may be helpful in informing their SRE policy and curriculum.

Participating SRE teachers will schedule one lesson (45 minutes) per class to provide study information, obtain consent and collect baseline measures. Pupils will be told that the study aims to evaluate teaching on STIs in their school, but not informed that there are two intervention arms. Pupils will also be told about the number and nature of assessments that will be made, and how their data will be protected and treated. They will be provided with a written participant information sheet and asked to sign a consent form.

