### Sample size calculation

The calculation is based on the primary research question. Power analysis using GPower 3.1.2 has indicated that 484 participants will provide 95% power to detect a small to medium effect of 0.3 [21] where α = 0.05. The effect size of 0.3 is based on a recent meta-analysis examining the effectiveness of interventions in changing risk appraisals, intentions and behaviour [22]. Due to the tendency for individuals within a cluster to be more similar to each other than those in other clusters, it is necessary to make adjustments to avoid an overestimation of power [23]. In order to obtain this adjusted sample size, the sample size determined by usual procedures is inflated by multiplication with a factor. This factor is known as the “design effect” and is calculated as:

$$1+\left(n–1\right)\mathrm{ICC}$$

where *n* is the average cluster size, and ICC is the intraclass correlation coefficient. The ICC for intention to use condoms between schools is not known but an estimate of 0.01 is reasonably conservative [23]. With ten schools and an average cluster size of 60 (×2 classes of 30 pupils), the design effect is:

$$1+\left(60–1\right)0.01=1.59$$

Accordingly the adjusted sample size is 484 × 1.59 = 770. We will over-recruit to allow for drop-out between the start of the study and the three month follow-up.

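### The design effect is taken from ten schools of 60 pupils (600), the requirement is 770, and nothing reconciles them; on the basis that yields 484, ten schools of 60 give about 90% power, not 95%

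*Protocol article*

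**What the plan says.** Everything needed is in the protocol article, mostly under Sample size calculation.

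- Unadjusted size: "484 participants will provide 95% power to detect a small to medium effect of 0.3", "where α = 0.05". Whether the test is one- or two-sided is not stated.
- Intraclass correlation: the section says the value between schools is unknown and that "an estimate of 0.01 is reasonably conservative".
- Layout behind the design effect: "With ten schools and an average cluster size of 60", each school supplying two classes of 30, which gives 1.59.
- Requirement: "Accordingly the adjusted sample size is 484 × 1.59 = 770".
- Drop-out: the section promises to recruit beyond this to cover losses up to follow-up, without a figure.

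Under Participant recruitment and baseline assessment the school count is repeated: "The study will take place in approximately ten schools across England". The Abstract also gives about ten. The same recruitment section provides a reserve list of schools, to replace schools that drop out.

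**The concern.** The layout that produces 1.59 supplies 600 pupils, and the next step requires 770. The two totals cannot describe the same trial. The gap is 170 pupils, or 22% of the requirement, before anyone declines or is lost.

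The gap cannot be closed by enlarging the schools alone, because the design effect rises with cluster size. Number of schools, pupils per school and total have to be solved together.

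The stated power of the primary comparison is at stake. A team that recruits ten schools with two classes each would stop at 600 and could still report the trial as having 95% power for an effect of 0.3.

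**Working it through.** **Inputs.** From Sample size calculation: standardised effect d = 0.3 (SD 1), alpha 0.05, power 95%, ICC 0.01, ten schools, 60 pupils per school, 484 unadjusted, 770 adjusted. Assumed: two arms of equal size (the ratio is not stated), no drop-out, and no gain from covariates (the section claims none).

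**Method.** Design effect DE = 1 + (m − 1) × ICC for m pupils per school. Effective size N_eff = N / DE. Power comes from the noncentral t distribution with noncentrality d × √(N_eff / 4).

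**1. The plan's own figures.**
- One-sided at 0.05, the smallest equal-arm total with at least 95% power is 242 per arm, 484 in all (power 0.951). This matches exactly.
- Two-sided at 0.05, the total needed is 580, and 484 gives 0.909. This does not match.
- DE = 1 + 59 × 0.01 = 1.59, and 484 × 1.59 = 769.56, rounded to 770. Both match.

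So 484 and 770 are arithmetically sound, on an unstated one-sided basis with individual-level degrees of freedom.

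**2. The stated layout.** 10 × 60 = 600, and 770 − 600 = 170 (22% of 770). N_eff = 600 / 1.59 = 377.4. Noncentrality = 0.3 × √(377.4 / 4) = 2.91. One-sided power is 0.897.

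**3. Ten schools filled to 770.** m = 77, DE = 1 + 76 × 0.01 = 1.76, N_eff = 770 / 1.76 = 437.5, and one-sided power is 0.932. The requirement itself moves to 484 × 1.76 = 852. Solving 10m / (0.99 + 0.01m) = 484 gives m = 92.9, so about 93 per school, or 930 in all.

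**4. Schools of 60 kept.** 770 / 60 = 12.8, so 13 schools (780 pupils, N_eff 490.6), or 14 for equal arms (840 pupils, N_eff 528.3).

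**5. All layouts on each basis (ICC 0.01).** Cluster-level degrees of freedom are the number of schools minus 2.

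| Layout | One-sided, individual df (reproduces 484) | Two-sided, individual df | One-sided, cluster df | Two-sided, cluster df |
|---|---|---|---|---|
| 10 × 60 | 0.897 | 0.829 | 0.844 (8 df) | 0.724 (8 df) |
| 10 × 77 | 0.932 | 0.880 | 0.887 (8 df) | 0.784 (8 df) |
| 10 × 93 | 0.951 | 0.910 | 0.913 (8 df) | 0.823 (8 df) |
| 13 × 60 | 0.953 | 0.913 | 0.928 (11 df) | 0.856 (11 df) |
| 14 × 60 | 0.964 | 0.931 | 0.945 (12 df) | 0.885 (12 df) |

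The 13-school row treats the arms as equal, which an odd number of schools cannot quite achieve, so it is slightly favourable.

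**6. ICC at which 600 would suffice.** 600 / 484 = 1.240, and (1.240 − 1) / 59 = 0.004. The section uses 0.01.

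**The case against.** A reader might infer that the design cannot deliver 95% power, or that its power is really 83% or 72%. The documents support neither in that form.

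- **Cannot is too strong.** The recruitment section says approximately ten schools, and asks co-ordinators to identify eligible classes without a limit of two per school. The 60 is an average used to obtain a design effect, and 770 is the figure adopted as the adjusted size. The operative target may well be 770 plus an allowance for drop-out. What is shown is an unreconciled text, not an inability to recruit.
- **The 83% and 72% mix separate issues.** On the one-sided basis that generates 484, the mismatch costs about five points (95% to 90%). The fall to 83% comes from moving to a two-sided test, and the fall to 72% from also using 8 degrees of freedom. Both questions are legitimate, but neither measures the gap between 600 and 770.
- **The obvious repairs depend on the basis.** Thirteen or 14 schools of 60, or ten of 93, pass 95% only one-sided with individual-level degrees of freedom.

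These three points stand, and they limit the claim. They do not remove it. Approximately ten stretches poorly to 13 schools before drop-out; over-recruitment and the reserve list are both tied to drop-out; and 77 pupils in each of ten schools still falls short. Nor is this a detail left to a fuller document: the article prints the whole calculation, and its input layout and output total disagree. Covariate adjustment might recover some power, but the section neither claims this nor gives a correlation from which to compute it.

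**Conclusion.** The point holds as an internal inconsistency that overstates power. Ten schools of 60 supply 600 pupils against a requirement of 770. On the only basis found to reproduce 484 (one-sided t test, alpha 0.05, individual-level degrees of freedom), they give about 90% power, so the chance of missing d = 0.3 is about 10% rather than 5%. Ten schools of 77 give about 93%.

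Two further uncertainties are separate from this mismatch. If the test is two-sided, 484 gives 91% even without clustering and ten schools of 60 give 83%. With 8 cluster-level degrees of freedom, ten schools of 60 give 84% one-sided and 72% two-sided.

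These figures rest on ICC 0.01, equal arms, no drop-out and no covariate gain. No ten-school layout with 60 or 77 pupils per school reaches 95% on any basis examined. That a null result would be misread as strong evidence of no effect is a reader's possible inference; the documents do not say so.

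**What to change.** State whether the primary test is one- or two-sided and whether the calculation uses individual- or cluster-level degrees of freedom. Then make number of schools, pupils per school, total and power agree on that one basis. Two routes are open.

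1. **No extra recruitment.** Keep about ten schools of 60, give the total as 600, and restate the power at ICC 0.01 as about 90% one-sided or 83% two-sided (84% or 72% on 8 degrees of freedom), adding that it is lower after drop-out. This takes only rewording; the price is a less favourable stated power.
2. **Keep 770 at 60 per school.** Replace ten with about 13 schools, or 14 for equal arms, before any allowance for drop-out. Note that this gives 95% only one-sided with individual-level degrees of freedom (two-sided, about 91% with 13 and 93% with 14). The cost is three or four more schools.

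Raising pupils per school within ten schools is consistent only if the design effect is recomputed: about 93 per school, 930 in all, on the one-sided basis.

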### Intervention

The intervention comprises a 45 minute lesson which is freely available in the form of a lesson plan and associated resources from the Health Protection Agency’s e-Bug website. E-bug is a school resource available across 10 EU countries covering microbes, their prevention, spread and treatment, including the spread of Sexually Transmitted infections. The lesson consists of four semi-interactive exercises, three of which are delivered using animated resources. These are accompanied by a lesson plan. The lesson aims to raise awareness of how chlamydia infection spreads internally causing damage in the short and long term. It challenges false reassurance provided by the belief that infection is easily treated by emphasising that treatment is unlikely to be sought in the absence of symptoms. It encourages pupils to personalise the true prevalence of infection, and highlights the fallibility of using overt characteristics to judge the risk posed by sexual partners. The lesson conveys the effectiveness of using condoms in preventing infection, and provides guidance on how to resist pressure to have unwanted sex, negotiate condom use, and correctly use condoms.

Behaviour Change Techniques (BCTs) used to deliver the lesson are:

•Information about health consequences

•Salience of consequences

•Anticipated regret

•Prompts/cues

•Instruction on how to perform a behaviour

•Demonstration of the behaviour

Whilst appropriate BCTs to target the selected determinants were identified at the time of intervention development using the most detailed and refined taxonomy available at that time [24], the BCTs above are those identified through a process of retrospective selection based on recent guidance (v0.1, 12.10.11) made available to the first author [personal communication; provided by University College London BCT Taxonomy team]. This guidance is based on the Behaviour Change Wheel method for intervention design [25]. The guidance refers to the most refined generic taxonomy available to date [26]. Work to develop this taxonomy is described in Michie and colleagues’ study protocol [27].

Further detail on the development and content of the lesson has been published elsewhere (link). Interested readers are directed to this report for further information.

Lessons in the control and experimental groups will be delivered by their usual timetabled SRE teacher. Those delivering the chlamydia lesson will be given minimal instruction with regards to delivery as all necessary information is contained within the lesson plan. Fidelity to the lesson plan will be assessed using a self-report checklist completed post-delivery (see Additional file 2).

On study completion, all schools allocated to the control group will be directed to the e-Bug website to enable them to download and deliver the chlamydia lesson if they wish providing the findings do not indicate that the lesson has any detrimental effects i.e. unfavourable changes in any of the primary or secondary outcome measures.

### Measures post delivery and at follow-up

Immediately following the lessons, a further set of measures will be taken (see Additional file 1). These will be a repeat of those taken at baseline. For those in the intervention arm, a few additional items will be included to allow for process evaluation. These items will measure participants’ enjoyment of the lesson, collect their opinions on the suitability and relevance of the content for their age, and ascertain the extent to which they felt they could relate to the characters and examples given. It will also determine whether participants felt the materials were engaging, and whether the delivery was sufficiently interactive. Items will be a mixture of fixed response and open-ended formats and will allow any necessary improvements to be made to the lesson following evaluation.

At follow-up, three months post delivery, measures of intention and use of condoms (during vaginal sex with casual sexual partners for whom STI status is unknown) will be taken (see Additional file 1).

A number of the lesson exercises are available as ‘games’ on the HPAs e-Bug website. For this reason, it will be necessary to ensure that those in the intervention group have not viewed these prior to delivery of the lesson, and that those in the control group have not viewed these both before or during the study period. Although we believe this to be unlikely, it will be necessary to determine this to ensure that contamination has not occurred and to control for any dose effect. This will be ascertained using a simple question within the follow-up measure. The reason for not choosing to screen for this at the time of baseline data collection is that doing this may inadvertently draw attention to existence of the ‘games’ and result in participants viewing them out of curiosity resulting in contamination. Data from individuals who viewed the resources prior to delivery of the lesson (intervention group) or before/during study period (control group) will be removed from the analysis.

All questionnaire items will be piloted with approximately five young people prior to use to assess ease of comprehension and the suitability of language. Changes will be made accordingly.

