Pupils will not be obliged to take part. Quizzes will be administered at the same time as questionnaires at all data collection time points to occupy pupils who do not wish to participate. Pupils will not be required to provide their name (participant responses at each time point will be linked through the demographic information supplied). Pupils will be seated in a manner that prevents classmates from overseeing their responses i.e. in exam conditions. All materials (questionnaires and quizzes) will be placed in a sealed envelope by the individual participants and posted into sealed boxes on completion. Teaching staff will not have access to these. Although parental consent will not be required, as parents of participating pupils will have already consented for their children to participate in SRE and related evaluation activities, a letter outlining the study and their child’s involvement will be sent to all parents through each school as a matter of courtesy. Parents will be given the opportunity to ‘opt-out’ their child at this point.

Baseline measures will be: Demographic information (age, date of birth, gender, and ethnicity), perceived likelihood, perceived severity, response efficacy, self-efficacy, past behaviour, and intention to use condoms during vaginal sex with casual sexual partners for whom STI status is unknown. Provisional measures to be taken at baseline, post-intervention and follow-up are provided in Additional file 1.

After the collection of baseline data, schools will be randomised to receive either the school’s usual teaching on STIs and the chlamydia lesson (intervention arm) or the school’s usual teaching on STIs alone (control arm). This enables the study to evaluate the effectiveness of the chlamydia lesson over and above usual practice. As described above, pupils will be blinded to intervention condition. It is not possible to blind teachers to intervention condition but they will be made aware of the importance of delivering teaching that is consistent with their usual practice. Researchers liaising with schools will offer the same guidance and level of support regardless of intervention condition.

As with all trials of this type, there is the potential for drop-out of whole schools during the study. We have no way of estimating the level of this. Drop-out due to unforeseen circumstances will be planned for and a reserve list of schools will be created to expedite the process of additional recruitment if required.

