### Statistical analysis

Prior to analysis, school codes will be removed from the data set by an independent researcher and intervention condition coded as A or B. This will blind analysts to intervention condition. Intention to treat analysis will be used so that data is used regardless of whether pupils are present or absent during the STI and chlamydia lessons in either of the intervention arms, and means are imputed for pupils with missing post-delivery and/or follow-up data. Whole classes or schools who drop-out during the study and don’t provide at least post-delivery data will be removed from the analysis.

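### Removing pupils who viewed the e-Bug games, on the strength of a follow-up answer and with a wider window in control, contradicts the stated intention-to-treat analysis and can bias the comparison

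*Protocol article*

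**What the plan says.** Some of the lesson exercises are openly available as games on the e-Bug website. To deal with contamination, the section Measures post delivery and at follow-up sets this rule: "Data from individuals who viewed the resources prior to delivery of the lesson (intervention group) or before/during study period (control group) will be removed". On how viewing is established, the same section says: "This will be ascertained using a simple question within the follow-up measure". The question is deliberately left out of the baseline questionnaire so as not to advertise the games. On frequency, the section says only: "Although we believe this to be unlikely, it will be necessary to determine this to ensure that contamination has not occurred".

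Randomisation comes earlier, under Participant recruitment and baseline assessment: "After the collection of baseline data, schools will be randomised to receive either" the lesson on top of usual teaching, or usual teaching alone.

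The Statistical analysis section describes a different population: "Intention to treat analysis will be used so that data is used regardless of whether pupils are present or absent" for the lessons, and "means are imputed for pupils with missing post-delivery and/or follow-up data". The only removal it provides for is at a higher level: "Whole classes or schools who drop-out during the study and don’t provide at least post-delivery data will be removed from the analysis". It does not mention pupils who viewed the games.

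**The concern.** The exclusion is decided after allocation, and its window differs by arm. Viewing between the lesson and follow-up leads to removal in control and has no consequence in the intervention arm. Pupils who go looking for chlamydia material of their own accord may differ from their classmates in condom use intention. If they do, the rule takes a selected group out of one arm only, and randomisation no longer protects the comparison. At stake is whether the primary result is the as-randomised effect that the Statistical analysis section promises.

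**Working it through.** **The two sections side by side**

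| Pupil | Intervention arm | Control arm |
|---|---|---|
| Viewed before the lesson, answers at follow-up | removed | removed |
| Viewed only after the lesson, answers at follow-up | kept | removed |
| Viewed at any time, no follow-up answer | kept, mean imputed | kept, mean imputed |
| Absent from the lesson | kept | kept |

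The second row is the asymmetry. The third shows that the rule reaches only pupils who complete follow-up: two control pupils who viewed alike are treated differently according to whether they were there to answer. The last row is what the intention-to-treat sentence protects. A pupil who missed the lesson stays in, while a control pupil who came across part of it goes out.

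**Effect on the control mean**

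Let v be the share of all control pupils who view only after the lesson and are identified at follow-up. Let s be their underlying difference in intention from other control pupils, in SD, and g the change that viewing itself causes. With non-viewers at mean m:

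- control mean with everyone kept: m + v(s + g)
- control mean had nobody been exposed: m + v·s
- control mean after removal: m

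Measured against the unexposed mean, removal shifts the comparison by v·s, in either direction according to the sign of s. Keeping everyone shifts it by v·g, towards no difference if viewing raises intention.

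**The measure straight after the lesson.** Intention is analysed at time two as well as at follow-up (To examine the effect of the intervention). A pupil who views the games later has already given the time-two answer, so g = 0 for that measure. Keeping later viewers costs nothing, and removing them leaves only the selection term v·s. The exclusion rule makes no distinction between time points.

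**Scale.** The protocol gives neither v nor s, so both are assumptions here: v = 1% to 10%, s = 0.3 to 0.5 SD. The yardstick is the planned effect of 0.3 (Sample size calculation).

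| v | s = 0.3 | s = 0.5 |
|---|---|---|
| 1% | 0.003 SD (1% of 0.3) | 0.005 SD (1.7%) |
| 5% | 0.015 SD (5%) | 0.025 SD (8.3%) |
| 10% | 0.03 SD (10%) | 0.05 SD (17%) |

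To set this against sampling error: the design effect reproduces as 1 + 59 × 0.01 = 1.59, and the adjusted size as 484 × 1.59 = 769.6, that is 770. The standard error of the difference is then √(4 × 1.59 / 770) = 0.091 SD. The top of the range is 0.05 / 0.091 = 0.55 of a standard error, and the bottom 0.003 / 0.091 = 0.03.

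**Cost of keeping everyone.** If a control viewer gains at most the full planned effect, dilution is at most v × 0.3: 0.003 SD at 1% viewing, 0.015 at 5% and 0.03 at 10%.

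**The case against.** The rule has a purpose. Control pupils who open the games receive part of the intervention, whereas for intervention pupils later viewing repeats what they were taught. Some difference in window is therefore inherent in defining contamination. That stands, and it is why the exclusion is worth keeping as a secondary look. It does not justify letting the exclusion define the only analysis population described, and it gives no reason to drop later viewers from a measure taken before they viewed.

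Intention to treat could be read narrowly here, as concerning lesson attendance only. But the same sentence keeps pupils with missing data, and the section's only removal rule is for whole classes or schools. The individual exclusion fits neither.

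A reader might infer that the rule does bias the result, most likely in the lesson's favour. The documents do not support this. If later viewers have lower underlying intention, the shift goes the other way; if viewing is unrelated to intention, there is none. A reader might also arrive at a third of the planned effect, from 20% viewing and a 0.5 SD difference (0.20 × 0.5 = 0.10; 0.10 / 0.3 = 33%). That figure fails on three counts. It counts pre-lesson viewers, who are removed in both arms. It treats any effect of viewing as bias, although removing that part undoes contamination. And its viewing rate sits badly with the protocol's expectation that viewing is unlikely. At 20%, moreover, keeping everyone could dilute by up to 0.20 × 0.3 = 0.06 SD, so a high rate cannot be used on one side of the argument only.

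Finally, the planned ANCOVA adjusts for demographics, time-one behaviour, and risk and coping appraisal. If the appraisals are baseline values, part of s may be absorbed. Baseline intention is not among the covariates named, so absorption cannot be assumed complete.

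**Conclusion.** The contradiction stands and depends on no assumption: individual pupils are removed after randomisation, on a follow-up answer, under a wider window in control, while the analysis section claims intention to treat and lists no such removal. No other part of the protocol reconciles the two. The bias is a possibility whose size and direction cannot be derived from the document. Under the assumed ranges it is 0.003 to 0.05 SD, or 1% to 17% of the planned 0.3, and it is negligible if viewing is as rare as expected. The case is clearest for the measure straight after the lesson, where removing later control viewers can only select. Rarity does not rescue the rule, since it then gains almost nothing. At equal viewing rates the possible dilution is of the same order as the possible selection bias or smaller, but dilution preserves the randomised comparison and its direction is known if viewing raises intention. The change is worth making, with modest practical impact expected.

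**What to change.** Replace the last sentence of the paragraph on the games in Measures post delivery and at follow-up. It should say that all pupils of randomised schools stay in the primary analysis in their allocated arm whether or not they report viewing, and that reported viewing will be tabulated by arm and by timing (before or after the lesson). The follow-up question must then capture timing in both arms, taking the school's usual STI teaching as the reference point in control.

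Move the exclusion, as currently defined, to a labelled sensitivity analysis, so that the contamination question is still answered. A second one could exclude only pre-lesson viewers in both arms. It cannot replace the first, because it keeps the control pupils exposed during the study. State that neither covers viewers without a follow-up answer.

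The cost is one rewritten sentence, possibly a small addition to the question, and one or two secondary analyses. The statistical price is the dilution bounded above: 0.003 SD at 1% viewing, 0.015 at 5% and 0.03 at 10%.
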